## Introduction

Skeletal muscle (SKM) metabolic function is dysregulated in type 2 diabetes mellitus (T2D). This dysregulation is associated with changes in muscle architecture which contribute to phenotypic frailty including slow gait speed, weakness, unintentional weight loss, fatigue, and low physical activity levels [1]. Glycemic dysregulation (e.g., insulin resistance) is a hallmark of T2D and contributes to SKM loss in adults with diabetes [2]. The pathogenic development of insulin resistance in T2D is multifaceted and includes, but is not limited to, mitochondrial dysfunction [3,4], decreased capillarization [5,6], and decreased SKM mass [7,8]. Evidence suggests that capillary networks and mitochondria-mediated metabolic alterations occur before the development of overt T2D; thus, it is critical to explore potential therapies in individuals with prediabetes to decrease T2D risk.

Exercise training is a key strategy to manage metabolic disease and decrease T2D risk [9]. While different exercise modalities improve SKM health across age groups, high intensity interval training (HIIT) can improve capillary density [10,11], mitochondrial content and function [12–14], and SKM mass [15] in older adults and those with T2D and obesity. However, exercise adherence is low [9,16,17]. In older adults at risk for T2D, compromised oxygen delivery and mitochondrial dysfunction [18] promote exercise intolerance, a factor contributing to low exercise adherence [19]. Alternative means to manage metabolic disease and improve metabolic health are needed, and heat therapy is a possible solution.

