The magnitude of angiogenic adaptations to local heat therapy (LHT) can be similar to whole-body heating [29], providing a foundation to support examination of the therapeutic potential of LHT. Although it has not been examined in individuals with prediabetes, a single lower body exposure to hot water circulation at 43°C for 90 min in patients with peripheral artery disease tended to improve walking performance [30]. Given these promising initial findings, LHT may be useful to improve muscle architecture (i.e., capillarization, mitochondria, muscle fiber CSA). Such changes could improve exercise tolerance by preconditioning the microenvironment of SKM, likely enhancing exercise adherence and improving subsequent exercise adaptations. Therefore, changes in the SKM with LHT alone, and with exercise training following LHT, may improve glycemic control and physical function, thereby decreasing risk for T2D and frailty, in older individuals.

Strong evidence supports the benefits of heat therapy on SKM and glycemic control. However, the efficacy of LHT to decrease risk for T2D and frailty in older adults with prediabetes has not been examined. Therefore, we developed the Heat and Exercise in Aging as Therapy (HEAT) study. This randomized, controlled clinical trial aims to evaluate the effectiveness of LHT among older adults with prediabetes using a two-phased approach. The aim of Phase 1 is to compare the effectiveness of LHT alone versus HIIT to improve muscle architecture, glycemic control, exercise capacity, and risk of frailty (Aim 1). The aim of Phase 2 is to assess whether a period of LHT preceding the initiation of HIIT improves exercise responsiveness, resulting in further improvements in SKM architecture, glycemic control, and risk of frailty (Aim 2). Given the practicality and ease of LHT application, findings can be easily translated to clinical recommendations.

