### Power analysis

A power analysis was performed using G*Power (version 3.1.9.4). Because capillary-fiber perimeter exchange index (CFPE) is a widely measured variable and an important component of anticipated adaptations, we used the results from Kim et al.[27] to power this study. They observed significantly greater CFPE with LHT vs CON (d > 1.5). We used a more conservative, d = 1.2 (reduced by 20%), because older adults might have a blunted response to LHT. We used the statistical analysis of Aim 1 to power the study because it involves more groups (three) and thus requires the largest number of participants. The one-way ANOVA with three groups (d = 1.2, f = 0.4899, α = 0.05) will require 45 total participants (15 per group) to achieve 80% power. This will be followed by two non-orthogonal planned contrasts (CON vs. LHT, LHT vs. HIIT). These *t*-*t*ests (d = 1.2, α = 0.05/2 [Bonferroni]) also require 15 participants per group to achieve 80% power. In the statistical analysis of Aim 2, only two of the three groups are included, leading to greater statistical power. The planned *t*-*t*est (d = 1.2, a = 0.05, 15 participants per group) will achieve 89% power. If needed, the one-way ANOVA with two groups (d = 1.2, a = 0.05, 15 participants per group) will also achieve 89% power. Comparing this number of participants per group to previously published work examining LHT and SKM mitochondria, capillarization, and size [26–28], 15 participants per group is a comparable estimate of sample size. Although not identical to our proposed work, sample sizes of 10 (within-subjects) [23] and 18 (9 per group, between-subjects) [31] were sufficient to detect improvements in glycemic control in overweight men and in obese women with polycystic ovarian syndrome, respectively, in response to whole-body heat therapy. Our power analysis and previously published research support a target sample size of 15 participants per group (CON, HIIT, and LHT). Accounting for a potential 18% attrition rate, we aim to enroll 18 participants per group (9 men, 9 women) for a total target enrollment of 54 participants.

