As an additional index of mitochondrial content, mitochondrial DNA (mtDNA; *DLOOP*:*B2M*) will be measured using qPCR [66]. DNA will be extracted from a small portion (~10 mg) of flash frozen SKM using a commercially available DNA extraction kit (DNeasy, Qiagen) and quantified (NanoDrop, ThermoFisher Scientific, Waltham, MA, USA). Previously validated [67] custom primers designed to span exon-exon junctions will be purchased (Integrated DNA Technologies, Coralville, IA, USA). Final reactions will contain gDNA (25 ng), primers (500 mM), SyBr green (Qiagen, Venlo, Netherlands), and nuclease-free water to 20 ul. All samples from a single participant will be analyzed on the same PCR plate and reactions will be run in triplicate.

Succinate dehydrogenase (SDH) activity will be measured using histochemistry in OCT-fixed samples according to previously published methods [67]. Briefly, samples will be cross-sectioned and incubated with phosphate buffer containing sodium succinate and nitro blue tetrazolium (NBT), washed with acetone and distilled water, and mounted. Images will be acquired using brightfield microscopy (Cytation C10) and analyzed using ImageJ and custom Python code that we will make available on GitHub.

Western blotting [39,40,68] will be used to detect the concentration of electron chain complexes in flash frozen SKM samples. Proteins will be separated using SDS-PAGE, electrophoretically transferred to a low-fluorescence PVDF membrane, and total protein imaged using a ChemiDoc MP (Bio-Rad Laboratories, Hercules, CA, USA). The membrane will be blocked and incubated overnight with commercially available primary antibodies against selected proteins in each electron transport chain complex (Total OXPHOS Human Antibody Cocktail, Abcam, UK) among other mitochondrial proteins. To provide insight into potential mechanism, primary antibodies against p-TRPV1 and TRPV1 will also be applied. Membranes will then be rinsed, incubated with the appropriate secondary antibodies, and imaged using enhanced chemiluminescence on a ChemiDoc MP (Bio-Rad Laboratories). Band density will be determined using Bio-Rad image analysis software and normalized to β actin.

Citrate synthase activity [69] will be measured in lysed flash frozen skeletal muscle samples in duplicate using a commercially available enzymatic assay (CS0720, Sigma-Aldrich, Burlington, MA, USA) and spectrophotometry.

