### Statistical analyses

All outcome measures at T1, T2, and T3 will be summarized using descriptive statistics. The study evaluates treatment efficacy by analyzing changes across three distinct time points (T1, T2, and T3). While the data are longitudinal, the primary aims focus on the magnitude of change within specific intervals. Therefore, the magnitude of change between time points for each outcome measure will be calculated for analyses.

To achieve Aim 1 (comparing LHT with CON and LHT with HIIT; k = 3), changes between T1 and T2 values (i.e., before and after Phase 1) for all muscle architecture outcomes, glycemic control outcomes, and frailty risk indicators will be calculated and checked for the assumption of normality using the Shapiro-Wilk test. An appropriate transformation will be conducted if normality is violated. Then, one-way ANOVA with three groups (CON, HIIT, LHT) will be run. This will be followed by two non-orthogonal planned contrasts (CON vs. LHT, LHT vs. HIIT). The Bonferroni correction will be used to control the familywise error rate.

To achieve Aim 2 (comparing LHT with CON after participants in both groups undergo HIIT during Phase 2 of the study; k = 2), changes between T2 and T3 values for all muscle architecture outcomes, glucose tolerance outcomes, and frailty risk indicators will be calculated and checked for the assumption of normality using the Shapiro-Wilk test. An appropriate transformation will be conducted if normality is violated. Then, a *t* test will be run to compare CON and LHT, and confidence intervals will be constructed to compare each variable between the two treatment groups. If improvements for participants in the LHT group from T1 to T2 make the absolute change from T2 to T3 smaller, we will also compare the combined improvements across both phases for the 2 treatment groups. Changes between T1 and T3 in muscle architecture outcomes, glucose tolerance outcomes, and frailty risk indicators will be calculated and transformed if needed. ANOVA analyses will be run and confidence intervals constructed to compare the combined improvements of each factor between the two treatment groups (CON and LHT). We can also employ a one-way ANCOVA for the T2-to-T3 analysis, including the T1-to-T2 change score as a covariate. This ANCOVA method can clarify the relationship between early-phase response and late-phase progress.

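### Western-blot outcomes are normalised to β-actin alone, which the protocol does not show to be unaffected by treatment, although total protein is already imaged on the same membrane

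*Protocol article*

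**What the plan says.** The blot method is in the protocol article under Assessment of muscle architecture, in the part on mitochondrial morphology and functional indices. Its purpose is given as: "Western blotting [39,40,68] will be used to detect the concentration of electron chain complexes in flash frozen SKM samples". Antibodies against further mitochondrial proteins and against p-TRPV1 and TRPV1 are also applied. Proteins are "electrophoretically transferred to a low-fluorescence PVDF membrane, and total protein imaged using a ChemiDoc MP". The quantification step is then: "Band density will be determined using Bio-Rad image analysis software and normalized to β actin". No other normaliser is named.

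The Introduction sets out what the treatments are expected to do to the tissue. For heat: "LHT may be useful to improve muscle architecture (i.e., capillarization, mitochondria, muscle fiber CSA". For exercise: "high intensity interval training (HIIT) can improve capillary density [10,11", with gains in mitochondria and muscle mass named in the same sentence.

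Statistical analyses, for Aim 1, takes "changes between T1 and T2 values (i.e., before and after Phase 1) for all muscle architecture outcomes, glycemic control outcomes, and frailty risk indicators" and compares the three arms by one-way ANOVA and two planned contrasts (CON vs LHT, LHT vs HIIT). The blots are described under muscle architecture, so they fall within this analysis. Aim 2 treats the T2-to-T3 changes in the same outcomes with a t test of LHT against CON.

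**The concern.** A loading control corrects for how much material was put in a lane. It does so only if treatment leaves the control protein alone. Here the denominator is one protein, measured after treatment, in tissue whose composition both active treatments are meant to alter. The article offers no evidence that β-actin is stable under heat or training.

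If β-actin moves by different amounts in different arms, that movement passes straight into the analysed change score and cannot be told apart from a change in the mitochondrial protein. Randomisation and blinding do not protect against this, because the shift arises after allocation. At stake is whether the blots show a mitochondrial response to LHT. The Discussion reports mixed mitochondrial findings with local heat and raises the idea of a temperature threshold, so a false null or a false gain could be misread.

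**Working it through.** **Inputs.** The normaliser, the total-protein image and the change-score analysis come from the sections cited above. The document gives no figure for a change in β-actin or for the expected gain in complex protein. Both are assumed below: true gain g = 0%, 20% or 40%; β-actin change a = -10% to +20%, with zero and a negative value included because the direction is unknown.

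**Formula.** With the baseline ratio set to 1, the apparent change is (1 + g)/(1 + a) - 1.

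| β-actin change | true 0% | true +20% | true +40% |
|---|---|---|---|
| -10% | +11.1% | +33.3% | +55.6% |
| 0% | 0% | +20.0% | +40.0% |
| +5% | -4.8% | +14.3% | +33.3% |
| +10% | -9.1% | +9.1% | +27.3% |
| +20% | -16.7% | 0% | +16.7% |

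Examples: 1.20/0.90 - 1 = +33.3%; 1.20/1.10 - 1 = +9.1%; 1.20/1.20 - 1 = 0%. With no β-actin change there is no bias. With no true effect, a shift alone creates an apparent one.

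**CON vs LHT.** Suppose CON changes in neither protein and LHT has a true 20% gain. A 10% β-actin rise in LHT leaves 9.1/20 = 45% of the true difference. A 10% fall inflates it to 33.3/20 = 167%.

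**LHT vs HIIT.** If both arms shift by the same a, the difference in apparent changes is the true difference divided by (1 + a). With true gains of 20% and 40% and a common 10% rise, the apparent difference is 27.3 - 9.1 = 18.2 points against a true 20, so 91% is kept. Serious bias in this contrast needs a shift that differs between the two arms.

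**What this could mean for power.** The plan's own figure first: for d = 1.2, two-sided alpha 0.025 and 15 per group, a noncentral t calculation gives 81.5%, in agreement with the stated 80%. That figure concerns the capillary index (CFPE), not the blots. If, as an illustration only, d = 1.2 also applied to a blot outcome with an unchanged SD and no change in CON, d would scale with the share of the gain retained:

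- True gain 20%, β-actin +5%, +10%, +20%: d = 0.86, 0.55, 0; power 50%, 21%, 3%.
- True gain 40%, the same shifts: d = 1.00, 0.82, 0.50; power 65%, 46%, 18%.
- True gain 20%, β-actin -10%: d = 1.2 × 33.3/20 = 2.0, an overstated effect.

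**The case against.** The strongest reply is that the case against β-actin is not in the document. Nothing there says which cells β-actin comes from in a muscle lysate, how it responds to heat or training, or that capillary growth raises it. The two steps can also coexist: total protein may serve as a loading or transfer check, and the blot methods are given by citation to papers not shown here. On that view the choice of normaliser is bench preference.

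Much of this stands, and it limits the claim. A reader might infer that capillary growth must raise β-actin, so that the more angiogenic arm is penalised and its mitochondrial gain understated or even reversed. The document does not support that. It expects muscle fibers to grow as well as capillaries, and if β-actin sat mainly outside the fibers, fiber growth would lower its share and overstate the gain. The net shift could be up, down or nil.

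A reader might also extend the concern to the trial's mitochondrial evidence as a whole. That does not hold either. Electron microscopy, mtDNA, succinate dehydrogenase histochemistry and citrate synthase activity do not use β-actin. A p-TRPV1/TRPV1 ratio formed within a lane would cancel the normaliser, although the article states no such ratio.

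The reply does not defend the choice itself. The normaliser is fixed in the text, not left open, and its stability is assumed without support in a trial designed to alter the tissue.

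**Conclusion.** The concern holds as a possible, avoidable bias in the blot outcomes, of unknown direction. Confirmed from the text: β-actin is the only stated normaliser, total protein is imaged on the same membrane without a stated quantitative use, and the treatments are expected to change tissue composition. Not confirmed: that β-actin moves at all. If it moves by about 10% in one arm only, an apparent gain of 9% or 33% in place of a true 20% is large enough to change the reading of a contrast with 15 per group. The sample size, which rests on CFPE, is unaffected. The point merits a change because the remedy is nearly free, not because bias has been shown.

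**What to change.** Replace the normalisation sentence with one saying that band density is normalised to total lane protein, taken from the total-protein image of the same membrane. That denominator sums over many proteins, so a treatment response in any single one matters less. Report β-actin by arm and time point only as a check. If β-actin is kept as the normaliser, the plan should instead give evidence that it does not change by arm or time.

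Cost: one sentence and a different quantification step on an image already planned. No new assay, tissue, participants or alpha is needed.

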### Data management

This clinical trial will generate a diverse set of scientific data from human participants. As described, these data will include demographic (e.g., age, sex, race, ethnicity) and anthropometric (e.g., body mass, body composition, height) information, clinical data (e.g., medical history, oral glucose tolerance test parameters, and responses to questionnaires), functional outcomes (e.g., exercise capacity, grip and leg strength, gait speed), and molecular measurements (e.g., muscle fiber cross-sectional area, capillarization, mitochondrial measures). These data will be collected from 54 older adults at risk for type 2 diabetes at multiple time points. Data collected at study visits will be entered into the two-way encrypted, HIPAA-compliant REDCap2 database and linked only by unique study ID codes, with personal identifiers stored separately in REDCap2. Biospecimens will be stored in a deidentified manner. Raw data generated from analysis of deidentified biospecimens will be stored on secure, cloud-based servers at Texas Tech University before uploading analysis-ready data into REDCap2.

Deidentified data from REDCap2 will be uploaded to the NIA Aging Research Biobank, a controlled-access data repository, where new unique IDs will be assigned, providing an additional layer of data protection. These data will be made available by request (submitted through the repository) on release of associated preprints or publication of associated manuscripts, and will remain accessible as long as the hosting repositories are supported. Metadata (e.g., protocols, data dictionary, etc.) will accompany each dataset. All custom code will be shared via GitHub with detailed documentation in a README file.

To ensure data quality, assessors are trained on all operating procedures. Standardized procedures and instruments with known reliability and validity are used where available. Duplicate measurements, range checks, and data validation (e.g., double entry where appropriate) are employed.

Anthropometric outcomes will be monitor weekly to ensure participants are not deviating from their normal routine and diet outside of the study. In addition, interim analyses for major measurements will be performed every 6 months from the beginning of the second year onwards.

### Statistical analyses

All outcome measures at T1, T2, and T3 will be summarized using descriptive statistics. The study evaluates treatment efficacy by analyzing changes across three distinct time points (T1, T2, and T3). While the data are longitudinal, the primary aims focus on the magnitude of change within specific intervals. Therefore, the magnitude of change between time points for each outcome measure will be calculated for analyses.

To achieve Aim 1 (comparing LHT with CON and LHT with HIIT; k = 3), changes between T1 and T2 values (i.e., before and after Phase 1) for all muscle architecture outcomes, glycemic control outcomes, and frailty risk indicators will be calculated and checked for the assumption of normality using the Shapiro-Wilk test. An appropriate transformation will be conducted if normality is violated. Then, one-way ANOVA with three groups (CON, HIIT, LHT) will be run. This will be followed by two non-orthogonal planned contrasts (CON vs. LHT, LHT vs. HIIT). The Bonferroni correction will be used to control the familywise error rate.

To achieve Aim 2 (comparing LHT with CON after participants in both groups undergo HIIT during Phase 2 of the study; k = 2), changes between T2 and T3 values for all muscle architecture outcomes, glucose tolerance outcomes, and frailty risk indicators will be calculated and checked for the assumption of normality using the Shapiro-Wilk test. An appropriate transformation will be conducted if normality is violated. Then, a *t* test will be run to compare CON and LHT, and confidence intervals will be constructed to compare each variable between the two treatment groups. If improvements for participants in the LHT group from T1 to T2 make the absolute change from T2 to T3 smaller, we will also compare the combined improvements across both phases for the 2 treatment groups. Changes between T1 and T3 in muscle architecture outcomes, glucose tolerance outcomes, and frailty risk indicators will be calculated and transformed if needed. ANOVA analyses will be run and confidence intervals constructed to compare the combined improvements of each factor between the two treatment groups (CON and LHT). We can also employ a one-way ANCOVA for the T2-to-T3 analysis, including the T1-to-T2 change score as a covariate. This ANCOVA method can clarify the relationship between early-phase response and late-phase progress.

Because the study utilizes balanced permuted block randomization, we expect key baseline characteristics, such as sex assigned at birth, age, and glucose tolerance, to be well-balanced across the three treatment groups. Our analysis will begin with a one-way ANOVA to evaluate primary treatment effects. To ensure the model is both parsimonious and robust, we will perform residual diagnostics by plotting residuals against various participant characteristics (demographic, clinical, and molecular). Non-random residual distributions will signal the need to include missing main effects, while diverging patterns across treatment levels will indicate potential interaction effects. These additional terms will be formally tested for significance before being integrated into the final model.

Note that integrating covariates into the model generally enhances the power to detect treatment effects by reducing error variance. Conversely, the power to detect interaction effects is usually low, as these effects typically exhibit smaller magnitudes and larger standard errors. Given that our sample size is determined based on a one-way ANOVA, all interaction analyses will be treated as exploratory.

While we anticipate complete data sets for primary outcomes assessed at T1, T2, and T3, there is a possibility of missing data. To address potential bias and maintain statistical power in the presence of potential missing data, we will employ Multiple Imputation by Chained Equations. We will generate several imputed datasets using all available baseline characteristics and previous timepoint values. Each dataset will be analyzed independently using the specified ANOVA or ANCOVA model, and the resulting estimates and standard errors will be pooled to produce a single inference according to Rubin’s Rules. This approach accounts for both within-imputation and between-imputation uncertainty.

To assess the robustness of our primary findings, a sensitivity analysis will be performed. While the primary analysis assumes data are Missing At Random, we will explore the impact of Missing Not At Random data. Specifically, we will apply a penalty to the imputed values of the treatment group to simulate a scenario where participants who dropped out had poorer outcomes than those who remained. If the treatment effect remains statistically significant under these conservative assumptions, the primary results will be considered robust.

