## Methods

### Study overview

The Heat and Exercise in Aging as Therapy (HEAT) clinical trial is a two-phase, randomized, sham-controlled, parallel-design study examining the effects of LHT alone, and LHT applied prior to HIIT, on SKM architecture, glycemic regulation, frailty risk, and exercise capacity in older adults with prediabetes (Clinical Trial NCT06580964 [https://clinicaltrials.gov/study/NCT06580964]). Eligible participants are randomized to one of three intervention groups for Phase 1 of the study: HIIT alone (HIIT group), LHT followed by HIIT (LHT group), or sham heat pad followed by HIIT (control [CON] group; thermoneutral temperature).

All primary outcome measures are assessed at baseline (timepoint [T]1), after Phase 1 (T2), and after Phase 2 (T3). Phase 1 consists of 12 weeks of the LHT intervention for the LHT and CON groups, or 12 weeks of high-intensity interval training for the HIIT group. Following T2, only participants in the LHT and CON groups progress to Phase 2, which involves 12 weeks of high-intensity interval training. Participants assigned to the HIIT group conclude their participation in the study after T2. The schedule of enrollment, interventions, and assessments is presented in **Fig 1**, in accordance with SPIRIT guidelines (**S1 Table**). An overview of the study design is presented in **Fig 2**. This study is approved by the Texas Tech University Institutional Review Board (IRB #2024-365) (**S1 File**). Any future modifications to the protocol will be submitted for IRB review and approval prior to implementation, reported to the study safety officer, and documented in the manual of procedures. The first participant will be enrolled on July 31^st^, 2025. Participant enrollment is expected to conclude by July 2028, data collection will be completed by February 2029, and study results are anticipated by December 2029.

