### Testing visits

#### Primary outcomes testing.

Testing for primary outcomes will be conducted at T1, T2, and T3. Each testing period will occur over two separate days. Day 1 includes a muscle biopsy and an oral glucose tolerance test (OGTT), and Day 2 includes assessments of physical function and exercise capacity. There will be 2–3 days between Testing Days 1 and 2. At T2 and T3, testing will begin 2 days following the last intervention session of each respective phase. For each testing visit (i.e., Day 1 and Day 2), participants will be instructed to refrain from certain medications (e.g., acetaminophen, NSAIDs) for 48 hours, avoid alcohol consumption for 24 hours, and maintain a 12-hour fast (nothing to eat or drink except water) prior to their scheduled assessments.

### Day 1

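### The Aim 1 Bonferroni correction covers the two contrasts of one outcome, not the many outcomes across three domains that the article treats as primary together

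*Protocol article*

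**What the plan says.** The Statistical analyses section says that, for Aim 1, T1-to-T2 changes "for all muscle architecture outcomes, glycemic control outcomes, and frailty risk indicators will be calculated". Each is then tested by one-way ANOVA, and "This will be followed by two non-orthogonal planned contrasts (CON vs. LHT, LHT vs. HIIT"). The next sentence is "The Bonferroni correction will be used to control the familywise error rate".

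The size of the correction is given only under Power analysis, where the contrasts are specified as ("d = 1.2, α = 0.05/2 [Bonferroni]) also require 15 participants per group to achieve 80% power". The variable used there is CFPE: "Because capillary-fiber perimeter exchange index (CFPE) is a widely measured variable and an important component of anticipated adaptations", it was chosen to size the trial. It is not named as the primary outcome.

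Primary status is given in the plural. The Study overview says "All primary outcome measures are assessed at baseline" and again at T2 and T3. Under Primary outcomes testing, "Day 1 includes a muscle biopsy and an oral glucose tolerance test (OGTT), and Day 2 includes assessments of physical function and exercise capacity". The missing-data paragraph of Statistical analyses also refers to primary outcomes in the plural. No outcome is called secondary, and only interaction analyses are labelled exploratory.

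For Aim 2, LHT and CON are compared on the same three domains, and the Power analysis section uses an alpha of 0.05 per outcome.

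**The concern.** A divisor of 2 pays for two contrasts on one variable, yet the same pair of contrasts is run on every outcome in three domains. A reader who takes the Bonferroni sentence at face value will think that the Aim 1 results as a whole carry a 5% error rate, and they do not.

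Because no outcome has priority, a positive result in any domain could be presented as a primary finding, and CFPE, the only variable with a power calculation, has no special standing. This matters because the article makes confirmatory use of the results: the missing-data plan calls findings robust if significance survives a penalty, and the Conclusions look ahead to clinical recommendations.

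**Working it through.** **1. The plan's own power figures (Power analysis section).** Inputs: d = 1.2, f = 0.4899, 15 per group, t-tests taken as two-sided.
- ANOVA: f = d × √(1/6) = 0.4899. Noncentrality f² × N = 0.24 × 45 = 10.8 on 2 and 42 df at 0.05 gives power 81.7% (N = 42 gives 78.6%).
- Contrast: noncentrality 1.2 × √(15/2) = 3.29 on 28 df at 0.05/2 = 0.025 gives 81.5% (14 per group gives 78.2%).
- Aim 2 t-test at 0.05: 88.7%.

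The stated 45, 15 per group, 80% and 89% all reproduce, each for one outcome.

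**2. Error within one outcome.** Two contrasts at 0.025 each give at most 0.05. Simulated under no effect, the rate is about 4.5–4.9%, or about 3.6% if the contrasts count only after a significant ANOVA. Within an outcome the rule works.

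**3. How many outcomes.** My count from Assessment of outcomes:
- Glycemic, 11: fasting, 1-hour, 2-hour and AUC glucose; fasting and AUC insulin; the sensitivity index; HOMA-IR; HOMA-β; C-Peptide Index; Insulinogenic Index.
- Muscle, about 14: two fiber areas, capillary density, CFPE, mitochondrial content and morphology by electron microscopy, mtDNA, SDH, five respiratory complexes, citrate synthase.
- Frailty, about 7: gait speed, grip, sit-to-stand, weight loss, fatigue, activity, overall category.

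11 + 14 + 7 = 32. Several overlap or are derived from one another, so I also use 25 and a deliberately low 16 (half of 32). The article gives neither a count nor correlations; both are assumptions.

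**4. Error across outcomes, Aim 1.** Simulation of 20,000 trials per setting: 3 groups of 15, normal data, no difference among any groups, pooled-error contrasts on 42 df with critical value t(0.9875; 42) = 2.32, equal correlation between outcomes. Chance of at least one false positive:

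| Outcomes | Rule | corr. 0 | 0.3 | 0.5 | 0.8 |
|---|---|---|---|---|---|
| 16 | either contrast | 53% | 46% | 37% | 21% |
| 16 | after significant ANOVA | 44% | 39% | 31% | 17% |
| 16 | LHT vs CON only | 33% | 28% | 22% | 12% |
| 25 | either contrast | 69% | 59% | 46% | 25% |
| 32 | either contrast | 78% | 66% | 52% | 27% |
| 32 | after significant ANOVA | 70% | 58% | 44% | 22% |
| 32 | LHT vs CON only | 56% | 44% | 34% | 16% |

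With one outcome per domain (three in all), the either-contrast rate is 13%, 12%, 12% and 9% at the same correlations. The upper bound under independence is 1 − 0.95³ = 14%.

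**5. Aim 2.** One comparison at 0.05 per outcome. With independent outcomes, 1 − 0.95¹⁶ = 56% and 1 − 0.95³² = 81%; correlation lowers these much as in the table.

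**6. Power if the correction covered the outcomes.** Bonferroni over m outcomes × 2 contrasts, d = 1.2:
- m = 3: alpha 0.05/6 = 0.0083; power 67.1% at 15 per group; 19 per group for 80%.
- m = 10: alpha 0.05/20 = 0.0025; power 49.9%; 24 per group for 80%.

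**The case against.** The Bonferroni sentence directly follows the description of the two contrasts, and the Power analysis section ties 0.05/2 to the same two. The natural family is therefore the pair of contrasts for one outcome, and for that family the statement is true. This stands: the sentence is too broad rather than false.

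A reader might infer that some LHT effect will more likely than not be declared even if LHT does nothing. The documents do not support that. The either-contrast rates assume that HIIT also does nothing; if HIIT works and LHT does not, an LHT–HIIT difference is real, and only LHT versus CON can yield a false LHT claim. That rate is 12–56% and mostly below one half. It counts differences in either direction; for 32 outcomes, a false result favoring LHT has a chance of about 33%, 23% and 16% at correlations 0, 0.3 and 0.5.

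Nor does any sentence declare each derived index a primary endpoint. The phrase about primary outcomes testing heads a visit description, and a few measures are described as additional or complementary. That leaves the count uncertain, but the error exceeds 5% even with three outcomes.

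Finally, this is a condensed article, and an unseen analysis plan may rank the endpoints. That would settle the ranking. It would not repair this text, which fixes the divisor at 2 and calls outcomes primary as a group; a correction across outcomes would contradict the stated power.

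**Conclusion.** The point holds as a fault in the scope of error control. Followed as written, Aim 1 controls error within each outcome and not across the outcomes treated as primary. Against a nominal 5%, the chance of at least one false positive is about 21–78% for 16–32 outcomes, about 17–70% with the ANOVA as a gate, and about 9–14% with one outcome per domain. These figures rest on a complete null, normal data, equal correlations of 0–0.8 and my count of outcomes; the direction does not depend on them, since every setting tried for the full set of contrasts exceeds 5%. Aim 2 adds a second uncorrected set of tests. The sample size is correct for a single outcome and for no more than that. The documents do not support saying that the Bonferroni sentence is plainly wrong or that a spurious LHT benefit is the likely result.

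**What to change.** - Name the T1-to-T2 change in CFPE, the variable on which the trial is powered, as the primary endpoint, with 0.05/2 covering its two contrasts.
- Reword the Bonferroni sentence so that it applies to those two contrasts only.
- If the sponsor wants confirmatory claims on glycemic control or physical function, let it select one key endpoint for each and test them after CFPE in a prespecified fixed order. Running the order separately within each contrast at 0.025 keeps Aim 1 at 5%.
- Report all other outcomes, including those of Aim 2, as secondary or exploratory, with estimates and confidence intervals and no confirmatory claim.

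The cost is wording in the protocol, analysis plan and registration, settled before any comparison by group is seen. Power for CFPE stays at 81.5% with 15 per group, and no participants are added. The downside is that fewer outcomes can be called confirmatory. If the sponsor prefers one primary endpoint per domain with Bonferroni over all three, that is also valid but needs 19 evaluable participants per group instead of 15.
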